### Date collection and management

2.6

All enrolled participants must complete a case observation form. All items on the observation form must be recorded carefully and in detail for all patients who have been screened and qualified to enter this trial and have completed the informed consent form. Full-text Analysis Set: For all cases that are randomized and grouped and received at least one treatment, the data of those cases in which the full treatment course is not observed are carried forward to the final results of the trial using the last observation data for intentional analysis of the main efficacy indicators. Per-Protocol Set: All cases that conformed to the trial protocol, had good compliance, did not take prohibited drugs during the trial, and completed the case report form, are statistically analyzed for all efficacy indicators. Safety Set: All cases that were randomized, completed at least one treatment, and had post-treatment safety evaluation data constituted the safety analysis population for this study.

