#### Recruitment

2.2.3

The study will be open to participants from all regions of China. Participants can enroll through the hospital's official website or be referred to our specialty clinics by healthcare professionals. The study will be promoted to healthcare providers, patient organizations, and directly to the public through the website and social media. We will also advertise in digital media. Participants will be assigned a screening ID and a member of the study team will conduct the initial eligibility screening. If they are interested in participating and potentially eligible, participants will be booked for the assessment. The inclusion assessment will be conducted under the supervision of a clinician. Additional information about the study will be provided immediately following this assessment. The assessor will perform final verification of the participant's eligibility criteria and sign the informed consent form. If the assessor is unsure of the eligibility of a potential participant, the principal investigator will have the final say. After signing the informed consent form, participants will be assigned a new study ID and will be randomized to a group. Treatment will begin within 1 week of randomization grouping. Where possible, excluded participants who still require clinical attention will be given routine treatment. Screening IDs and reasons for exclusion will be recorded for use in the final study report.

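### Last observation carried forward is the only stated missing-data rule for the main efficacy outcomes, the cytokines are assigned only a per-protocol set, and the safety set depends on later data

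*Protocol article*

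**What the plan says.** Section 2.6 of the protocol article defines three analysis sets.

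- **Full set.** Membership: "For all cases that are randomized and grouped and received at least one treatment". For incomplete courses, "the data of those cases in which the full treatment course is not observed are carried forward to the final results of the trial", with the last observation as the value, and the set is used "for intentional analysis of the main efficacy indicators".
- **Per-protocol set.** Membership: "All cases that conformed to the trial protocol, had good compliance, did not take prohibited drugs during the trial, and completed the case report form". This set is used for all efficacy indicators.
- **Safety set.** Membership: "All cases that were randomized, completed at least one treatment, and had post-treatment safety evaluation data".

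Section 2.5.1 lists NIH-CPSI with a sexual function index, and the urodynamic indexes, as primary. Table 1 schedules NIH-CPSI at registration, in weeks 1 to 4 and one week after completion. The urodynamic indexes (section 2.5.1) and the serum cytokines (section 2.5.2, secondary) are taken before and after treatment. Section 2.7 plans Bonferroni-corrected pairwise comparisons and a repeated-measures analysis of NIH-CPSI. On timing, section 2.2.3 says: "Treatment will begin within 1 week of randomization grouping".

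**The concern.** LOCF treats a patient's last recorded score as the final one. That is reasonable only if scores have stopped moving by the time the patient leaves. Here NIH-CPSI is measured weekly during a course that is meant to lower it, so an early score is a poor stand-in for the final one. For the urodynamic indexes the only earlier value is the baseline, so a drop-out is recorded as having changed by exactly zero.

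The three arms differ in burden: eight acupuncture sessions, a nightly suppository, or both. Unequal drop-out is therefore plausible, although the article does not forecast it. If it occurs, part of the drop-out difference is converted into an efficacy difference, and the filled-in values are analysed as if observed.

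Two further rules in the same section select patients after randomisation. For the cytokines, which section 3 makes part of the study aim, the only set named is one of compliers with completed forms. For safety, a treated patient without later safety data leaves the denominator.

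**Working it through.** The article gives no sample size, SD, drop-out rate or alpha, so there is no planned figure to reproduce. Every input below except the number of weeks is an assumption.

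**1. False difference under LOCF with no true difference.** Both arms fall by D points in a straight line over 4 weeks. Drop-out is p1 in one arm and p2 in the other, all after week k. A drop-out misses L = D × (4 − k)/4 points of the fall, so

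false difference b = (p2 − p1) × L.

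- Equal drop-out: p2 − p1 = 0, so b = 0.
- 5% v 20%, D = 4: 0.15 × 3 = 0.45 (week 1); 0.15 × 2 = 0.30 (week 2).
- 5% v 20%, D = 10: 0.15 × 7.5 = 1.125 (week 1); 0.15 × 5 = 0.75 (week 2).

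**2. Rejection rate.** Assume SD 6, correlation 0.6 between first and last score, and 40 per arm. The variance of the change is 2 × 36 × (1 − 0.6) = 28.8. Mixing drop-outs with completers adds p(1 − p)L² in each arm.

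For D = 10 and week 1:
- arm variances: 28.8 + 0.0475 × 56.25 = 31.47 and 28.8 + 0.16 × 56.25 = 37.80
- SE = √((31.47 + 37.80)/40) = 1.316
- b/SE = 1.125/1.316 = 0.855
- rejection = Φ(−z + b/SE) + Φ(−z − b/SE), with z = 1.960 for an unadjusted 5% test and z = 2.394 for 5%/3 = 1.7% (Bonferroni over three pairs)

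| D | Exit after | b (points) | SE | Rejects at 5% | Rejects at 1.7% |
|---|---|---|---|---|---|
| 4 | week 2 | 0.30 | 1.209 | 5.7% | 2.0% |
| 4 | week 1 | 0.45 | 1.219 | 6.6% | 2.4% |
| 10 | week 2 | 0.75 | 1.253 | 9.2% | 3.8% |
| 10 | week 1 | 1.125 | 1.316 | 13.7% | 6.2% |

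Simulation of the two 10-point rows agrees: 9.1% and 13.4% for the unadjusted test, 3.6% and 5.9% per pair after correction. With 15% drop-out in both arms after week 1, simulation gives no bias and 5.3% rejection.

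**3. Shrinkage under equal drop-out.** Suppose a true difference grows in a straight line and drop-outs leave evenly after weeks 0 to 3. The mean share missed is (1 + 0.75 + 0.5 + 0.25)/4 = 0.625, so the share kept is 1 − 0.625 × drop-out: 94% at 10%, 88% at 20% and 81% at 30%.

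**4. Outcomes with one post-treatment value.** Here k = 0 and L is the whole change. At 5% v 20% the false difference is 0.15 of the mean change, whatever the scale.

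**5. Sets.** The full set is tied to the main efficacy indicators and the per-protocol set to all of them. No other set is mentioned, so per-protocol is the only one assigned to the cytokines. For safety, suppose a true event rate of 10%, with 40% of those patients leaving and none of those leavers having a safety record, while everyone else has one. The observed rate is 0.10 × 0.6/(1 − 0.10 × 0.4) = 0.06/0.96 = 6.25%. This is an extreme case.

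**The case against.** The strongest reply is that nothing in the article shows drop-out will be unequal or early, and that the size depends on this. That stands: with equal drop-out there is no false difference, and with a 4-point fall the inflation is small. An unadjusted two-arm test is also not the planned one. Section 2.7 corrects pairwise comparisons, so 9% to 13% should not be read as this plan's per-comparison error rates. The corrected rates are lower, but still above the nominal 1.7%.

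On the sets, a condensed article may leave secondary populations to a separate analysis plan. A reader might infer that the cytokines will be analysed only per protocol. The text does not say so; it only names no other set. The per-protocol analysis also covers the primary outcomes, so LOCF is not their only analysis, although that alternative is itself selected after randomisation.

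A reader might also infer that anyone who stops during the first session, or leaves after a reaction, is dropped from the safety set. That depends on what completing a treatment and post-treatment mean. If post-treatment means after the first session, a recorded reaction is itself safety data and the patient stays in. On either reading, treated patients with no later data are left out.

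Finally, requiring at least one treatment is a common modified intention-to-treat rule. Treatment may start up to a week after allocation and patients can tell needles from a suppository, so non-starters could differ by arm. With no number of non-starters given, this is a minor point.

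**Conclusion.** The concern holds as a risk built into stated rules. The article fixes LOCF itself and offers nothing in its place, so this is not a detail left to another document. LOCF suits neither the weekly NIH-CPSI nor the before-and-after urodynamic indexes.

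A reader might conclude that the results will be biased, or in a known direction. The documents do not support that, because the effect depends on drop-out by arm, which is not given. Under the assumptions shown and no true difference, the false difference runs from 0 (equal drop-out) through 0.3 to 0.5 points (5% v 20%, 4-point fall) to 0.7 to 1.1 points (5% v 20%, 10-point fall). In the last case an unadjusted 5% test rejects about 9% to 13% of the time, and 3.6% to 5.9% per pair after Bonferroni correction. Equal drop-out of 10% to 30% would instead leave about 94% to 81% of a true, growing difference.

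The cytokine and safety-set points are secondary but also rest on stated wording. The exclusion of non-starters is minor.

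**What to change.** - **NIH-CPSI:** replace LOCF with a mixed model for repeated measures on the weekly scores already scheduled, in randomised patients as assigned. Add a delta-adjusted or reference-based sensitivity analysis.
- **Urodynamics and cytokines:** with one post-treatment value, a weekly model does not help. Use ANCOVA adjusted for baseline, with multiple imputation.
- **Sets:** analyse secondary efficacy in the full set as well and label the per-protocol analysis supportive. Including randomised non-starters in the full set is desirable but minor.
- **Safety:** define the set as all patients who received any study treatment, with no requirement for later data.

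The cost is a rewrite of sections 2.6 and 2.7, a little more analysis work and slightly wider intervals. Section 2.7 already plans a repeated-measures analysis, and the weekly scores are already scheduled. Continuing to collect NIH-CPSI after treatment stops is optional; it is a change to data collection, not only to wording, and adds modest effort.

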### Statistical analyses

2.7

The case information collected by Excel will be imported into SPSS 25.0 statistical software to establish the analysis database and complete the statistical analysis of the data. Normality test will be performed by Kolmogorov-Smirnov method; chi-square test will be performed by Levene method. The measurement data conform to normal distribution and will be described by means and standard deviations, and comparisons between groups will be made by one-way ANOVA ANOVA or independent samples *t*-test; two-way comparisons will be made by Bonferroni method corrected *P*-value; not conforming to normal distribution, the measurement data will be described by medians and quartiles, and comparisons between groups will be made by Kruskal-Wallis method test or The Mann-Whitney *U* test will be used for comparison between groups, and the Dunnett's method will be used for comparison between two groups. The dichotomous data will be expressed as composition ratio and frequency in describing the distribution pattern, and the chi-square test and exact Fisher test will be used for comparison between groups. NIH-CPSI scores, mean urine flow rate and maximum urine flow rate will be compared between the two groups of patients at different time points using repeated measures ANOVA-generalized linear model equations.

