**Methods::**

The study is a single-blind, parallel-group, randomized controlled clinical trial consisting of a 4-to-6-week treatment period and a 6-month follow-up period. Included participants will be randomized into three groups and given a treatment regimen of acupuncture, qianliean suppository, respectively. Patients in each group will be treated for 1 month as a course of treatment. The clinical efficacy and changes in inflammatory factor levels in each group will be assessed at the end of treatment.

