## Introduction

1

Chronic prostatitis (CP) is the most common genitourinary disorder in adult men. Surveys have shown that 35% to 50% of men will be affected by prostatitis at some point in their lives.^[1]^ CP is a difficult class of disease to treat. The typical clinical presentation of the disease is prolonged and recurrent pain in the pelvic region. The duration of the painful discomfort is often greater than 3 months. Some patients also often have varying degrees of urinary symptoms and sexual dysfunction.^[2,3]^ CP is a complex and protracted disease, which is difficult to treat. It brings serious psychological and economic burdens to patients and seriously affects their quality of life. Some patients even develop severe anxiety and depression as a result, which in turn leads to many social problems. Currently, it has attracted the attention of clinicians in various countries. In recent years, Western medical treatment of CP has gradually changed from antibiotics to a combination of α-blockers, androgens, anti-anxiety and antidepressants, and the efficacy has improved, but patients are still not satisfied with the treatment effect.^[4]^ Therefore, it is often necessary to continuously increase the dose of medication in order to achieve a more satisfactory therapeutic effect. This may cause serious adverse effects and affect patient compliance with treatment. Based on the above status, more effective treatment modalities need to be further explored.^[5]^ As a traditional treatment modality inherited for thousands of years, acupuncture has been valued and widely used in the clinical treatment of CP in recent years.^[6]^ This treatment modality can improve the quality of life by promoting neuromuscular excitability and by enhancing the contractility of urethral muscles and perineal muscles. qianliean suppository is a topical preparation made from several Chinese herbs with the effects of clearing heat, relieving dampness, promoting laxity, resolving siltation, dispersing nodules, and relieving pain. This study will investigate the therapeutic effects of acupuncture combined with qianliean suppository on CP, aiming to provide valuable evidence-based medical evidence for clinicians.

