### Interventions

2.4

(1)Acupuncture group: selected acupoints: *Shensu, Zhongliao, Huiyang, and Sanyinjiao* (all taken bilaterally). The acupuncture points will be positioned with reference to the 2006 National Standard of the People's Republic of China (GB/T 12346–2006) “Name and Positioning of Acupuncture Points”. After local sterilization of the acupoints, Shensu and Sanyinjiao will be needled with 0.3 × 40 mm milli-needles at a depth of 20 to 30 mm; Zhongliao and Huiyang will be needled with 0.3 × 75 mm milli-needles at a depth of 50 to 70 mm; the needles will be retained for 30 minutes.(2)Qianliean suppository group: use prostate suppository (National Drug Administration Z10980066, specification 2g × 5 s) for treatment. This product is brown or black-brown torpedo type suppository. Usage: The drug is inserted into the anus at night before bedtime, placed at a depth of 2 cm, 1 capsule each time, once a day. The ingredients of this drug are: extracts of Chinese herbs such as *Huangbai, Huzhang, Zhizi, Dahuang, Zelan, Maodongqing, Wuzhuyu, Weilingxian, Shichangpu and Lizihe*. Precautions for use: After the suppository is inserted into the anus, if there are uncomfortable symptoms such as bowel movement, abdominal pain and diarrhea, the method of use can be improved, such as applying vegetable oil outside the suppository or placing the suppository deeper, after the rectum adapts, the above symptoms can be reduced or disappear.(3)Combination therapy group: The treatment methods of (1) and (2) are combined.

Patients in each of the above groups will be treated for 1 month as a course of treatment. Patients in each group will be asked to abstain from sexual intercourse during the treatment period, to ensure the cleanliness of the perineal area, to observe the adverse reactions and to provide timely and effective treatment to ensure the treatment effect.

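### Cheap improvement, not an error: with exactly three arms, Shaffer's step-down keeps the 5% familywise error and never loses a Bonferroni rejection in the normal-data pairwise comparisons of section 2.7

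*Protocol article*

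**What the plan says.** The abstract states that "Included participants will be randomized into three groups". Section 2.4 defines them as acupuncture, Qianliean suppository, and a third arm in which "The treatment methods of (1) and (2) are combined". The Introduction gives the aim as studying the "therapeutic effects of acupuncture combined with qianliean suppository on CP".

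Section 2.7 sets different rules for different data:

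- **Normally distributed measurements:** one-way ANOVA or a t-test, after which "two-way comparisons will be made by Bonferroni method corrected" P-values.
- **Non-normal measurements:** Kruskal-Wallis or Mann-Whitney, after which "the Dunnett's method will be used for comparison between two groups".
- **Dichotomous data:** chi-square or Fisher's exact test, with no pairwise correction named.
- **Repeated measurements:** "NIH-CPSI scores, mean urine flow rate and maximum urine flow rate will be compared between the two groups of patients at different time points", by a repeated-measures model, again with no pairwise correction named.

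The article gives no alpha, sidedness, allocation ratio, effect size, standard deviation, power or sample size. Section 2.1 says only that the sample will be adequate.

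**The concern.** Three arms give three pairwise comparisons. At an assumed overall 0.05, Bonferroni tests each at 0.05/3 = 0.0167, however the other comparisons turn out. Three means obey a logical constraint that Bonferroni ignores: the number of true equalities can be 3, 1 or 0, but never exactly 2, because two equalities imply the third. After one genuine difference has been declared, the other two comparisons need no further correction.

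What is at stake is power, not validity. The only comparators are the two components of the combination, so showing that the combination adds to each of them needs two significant contrasts. A flat correction costs most on such a joint result.

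**Working it through.** The plan has no power or sample-size figure to reproduce. Everything below is an illustration under stated assumptions.

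**Inputs**

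- Three arms, hence three pairs (abstract; section 2.4).
- Bonferroni for normal-data pairs (section 2.7).
- Assumed: two-sided alpha 0.05; 1:1:1 allocation; the same true effect of the combination against each single arm, so the single arms are equal; pooled-variance t-tests; uncorrected power per contrast of 50% to 95%; 20 to 60 men per arm, plus the large-sample limit.

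**Step 1: cost on a single contrast (large sample).** Power of 80% at an uncorrected 0.05 needs a true difference of 1.960 + 0.842 = 2.80 standard errors. The Bonferroni critical value at 0.0167 is 2.394. Power becomes Φ(2.80 − 2.394) = Φ(0.41) = 66%.

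**Step 2: the alternative rule.** Order the three P-values. If 3 × the smallest is at most 0.05, reject that null hypothesis and judge the other two at 0.05. If not, reject nothing.

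**Step 3: error control (1,000,000 simulated trials per setting).**

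- All three arms equal: chance of any false rejection 4.35% under both rules, since the first step is the same.
- One arm different, the other two equal: false rejection of the one true equality under Shaffer is 2.8% to 5.0%, depending on how far the third arm lies from the others. Under Bonferroni it is about 1.7%.
- No simulated trial was significant on both combination contrasts under Bonferroni but not under Shaffer.

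**Step 4: chance that the combination is significant against both single treatments.**

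| Uncorrected power per contrast | Setting | Bonferroni | Shaffer |
|---|---|---|---|
| 50% | 30 per arm | 18% | 29% |
| 80% | 30 per arm | 49% | 65% |
| 95% | 30 per arm | 80% | 89% |
| 50% | large sample | 18% | 30% |
| 70% | large sample | 37% | 53% |
| 80% | large sample | 51% | 66% |
| 90% | large sample | 69% | 82% |
| 95% | large sample | 81% | 90% |

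With uncorrected power held at 80%, the number per arm hardly matters: 48.1% against 64.0% with 20 per arm, and 49.8% against 65.4% with 60. The assumed power is what moves the result. The gain is about 9 to 16 percentage points over this range.

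**Step 5: Holm for comparison.** With 80% uncorrected power and 30 per arm, Holm gives 56%. It recovers less than half of the gap between 49% and 65%.

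**Step 6: mismatch with intervals.** Every Bonferroni success is also a Shaffer success. The share of Shaffer successes in which at least one Bonferroni-width interval includes zero is therefore 1 − (Bonferroni/Shaffer). With 80% uncorrected power and 30 per arm this is 1 − 48.9/64.7 = 24%.

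**The case against.** The strongest reply is that Bonferroni after a three-group ANOVA is standard and valid, so nothing is wrong. That stands: no error rate is inflated, and anyone who reads this as a flaw in validity goes too far. It is also fair that Bonferroni is stricter on a single true equality (about 1.7% against up to 5.0%). Both meet the 5% standard.

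Three further inferences are tempting, and the article does not support them:

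- **That this trial's power falls from 65% to 49%.** Those figures need 80% uncorrected power per contrast and the other assumptions above. The article states none of them.
- **That the clause governs the main outcome.** The Discussion names NIH-CPSI as the main index, but section 2.7 sends its scores over time to a repeated-measures model with no named correction. The Bonferroni clause does not cover the non-normal branch either.
- **That significance against both single treatments is the success rule.** No such rule is stated. If it were the sole claim, both contrasts could be tested at 0.05 with no adjustment. In the 80%, 30-per-arm setting that gives about 68%, against 65% for Shaffer. Shaffer suits a plan that, like this one, corrects all the pairwise comparisons.

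The interval objection also stands in part. Step-down tests have no simple matching simultaneous intervals, and Bonferroni-width intervals beside them could contradict the tests. Section 2.7 promises corrected P-values and mentions no intervals, so the change breaks nothing that is planned.

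**Conclusion.** The point holds as a low-cost gain in efficiency, limited to the pairwise comparisons that follow one-way ANOVA of normally distributed measurements. That Shaffer's rule controls familywise error and rejects whatever Bonferroni rejects follows from having exactly three arms; it does not depend on the power assumptions. The size of the gain does depend on them. Under two-sided 0.05, equal allocation and equal effects against both single arms, it is about 9 to 16 points on the joint result for uncorrected power of 50% to 95%. How far this matters for the trial's conclusions depends on which outcomes are analysed through this branch, which the article leaves partly open.

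**What to change.** In section 2.7, replace the Bonferroni wording for normally distributed data with, for example: *After one-way ANOVA of normally distributed measurements, the three pairwise P-values will be adjusted by Shaffer's step-down procedure: the smallest is multiplied by 3 and, if the result is at most 0.05, the other two are each judged at 0.05; otherwise no pair is declared different.* State the overall alpha and that the rule applies to these comparisons only. Holm's procedure is a simpler but weaker choice.

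If confidence intervals are reported, label them as unadjusted or say that they do not correspond to the step-down tests.

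The cost is one sentence and a hand calculation on three P-values, with no extra patients or data. The loss is the simple simultaneous intervals that match Bonferroni tests. The change should be made before outcome data are seen.

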### Study design and setting

2.1

The study is a single-blind, parallel-group, randomized controlled clinical trial consisting of a 4- to 6-week intervention and a 6-month follow-up period. The study will be conducted at one site, the Affiliated Hospital of Shaanxi University of Chinese Medicine. A brief flow chart of the entire study is shown in Figure 1. This study will adopt a parallel controlled design approach. We will ensure a balance of baseline data across groups by having an adequate sample size and a completely randomized grouping method. The study will be approved by the Ethics Committee of the Affiliated Hospital of Shaanxi University of Chinese Medicine. We will not begin recruiting participants until ethics committee approval has been obtained.

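### For non-normal outcomes the plan follows Kruskal-Wallis with Dunnett's method, a normal-theory comparison of means against a reference arm that the protocol never designates

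*Protocol article*

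**What the plan says.** Section 2.7 of the protocol article chooses the analysis of continuous outcomes by a Kolmogorov-Smirnov test.

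- **Normal branch:** means and SDs, one-way ANOVA or t-test, then "two-way comparisons will be made by Bonferroni method corrected" P values.
- **Non-normal branch:** medians and quartiles, Kruskal-Wallis or Mann-Whitney U, then "the Dunnett's method will be used for comparison between two groups".
- **Dichotomous data:** "the chi-square test and exact Fisher test will be used for comparison between groups". No pairwise step is described.
- **Repeated measures:** NIH-CPSI and the mean and maximum urine flow rates at different time points go to a repeated-measures ANOVA / generalized linear model.

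On the arms, the abstract says "Included participants will be randomized into three groups". Section 2.4 lists an acupuncture arm, a suppository arm, and a third: "Combination therapy group: The treatment methods of (1) and (2) are combined". Section 2.1 says "This study will adopt a parallel controlled design approach", but no section names one arm as control or reference.

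**The concern.** The pairwise step does not fit the branch in which it stands, for three reasons.

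1. Dunnett's method tests differences in means with a pooled variance under normality. It is called on only after normality has been rejected, and it follows a rank test reported with medians.
2. It is a many-to-one procedure and needs a reference arm. All three arms are active and none is designated, so the comparison set is undefined.
3. The normal branch uses Bonferroni-corrected pairwise comparisons. A preliminary normality test would therefore decide which hypotheses are tested as well as how.

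At stake are power on strongly skewed outcomes and a freedom to choose comparisons that the plan should close before data are seen. The usual rank-based follow-up to Kruskal-Wallis is Dunn's test. The similar name suggests a slip, but an analyst who follows the text would run a different procedure.

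**Working it through.** The article states no sample size, alpha or SD, so there is no figure to reproduce. From the document come three arms, no named reference, and the methods in 2.7. Assumed for illustration are two-sided alpha 0.05, 40 per arm, and lognormal data with only the combination arm shifted.

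**Step 1: pairs covered.** Three arms give 3 × 2 / 2 = 3 pairs. Dunnett's method makes 3 − 1 = 2 comparisons once a reference is named. One pair is always outside it, and the text does not say which.

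**Step 2: what if it is applied to every pair?** The large-sample two-sided Dunnett critical value for two comparisons against one reference is about 2.21 (2,000,000 simulated draws, equal arms). Using 2.21 for all three pairs gives a family error of 0.069 under the global null, not 0.05.

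**Step 3: power under skew.** The statistics compared are:

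- Dunnett: t = (difference in means) / √(s² × 2/n), with pooled s² on 120 − 3 = 117 degrees of freedom.
- Dunn: z = (difference in mean ranks) / √(N(N+1)/12 × 2/n). With N = 120 and n = 40 the denominator is √(1210 × 0.05) = √60.5 = 7.78. Bonferroni over two comparisons gives a critical value of 2.241.

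Simulated power for one contrast of the combination arm with a single treatment:

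| Log-SD | Log-shift | Dunnett | Dunn |
|---|---|---|---|
| 1 | +0.65 | 60% | 70% |
| 1 | −0.65 | 41% | 71% |
| 0.5 | +0.325 | 72% | 71% |

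The shift is 0.65 log-SDs in size in every row (0.65/1 = 0.325/0.5). Ranks do not change under a monotone transformation, so Dunn's power stays at 70–71%. Dunnett's depends on the skew and on the direction of the effect. The downward case is the relevant one if treatment lowers cytokines.

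**Step 4: false positives.** Under the null at log-SD 1 and 40 per arm, Dunnett's family error is about 4%. Skew alone does not inflate it.

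**Step 5: effect of correcting for three pairs.** The table uses a two-comparison correction for both methods. Over three pairs the critical value rises from 2.241 to 2.394. Starting from 70% power, Φ(0.524 + 2.241 − 2.394) = Φ(0.371) = 64%. On this approximation Dunn's test over all three pairs still exceeds Dunnett's 60% and 41% at log-SD 1. At log-SD 0.5 it falls below Dunnett's 72%, but Dunnett would then be testing only two pairs.

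**Step 6: reach.** NIH-CPSI, which the Discussion calls the main outcome index, and flow rates over time are assigned to the repeated-measures model. What remains for this wording is mainly IL-1β, IL-6 and TNF-α (secondary, 2.5.2) and other continuous measures compared at one time point.

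**The case against.** The strongest reply is that this is a naming slip. The sentence speaks of comparing two groups, which suggests pairwise tests, and the same section attributes a chi-square test to Levene, which is plainly a translation error. That is plausible. It makes the remedy easy, but the method is still named wrongly, and a separate analysis plan does not cure an explicit statement.

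A second reply is that Dunnett's T3 or C was meant. Those are all-pairs methods and would remove the missing-reference problem, but they still compare means.

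A third is that any active arm could serve as reference. That is true: the trial does not lack a possible reference; the plan fails to designate one.

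A fourth is that the harm is limited. This stands. The power loss disappears at moderate skew with an upward shift, and family error under the skewed null stays below 5%.

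A reader might also infer three stronger points that the document does not support.

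- *Pairwise tests on the effective rate are left uncorrected.* Section 2.7 prescribes no pairwise binary tests, and an article may leave that step to the full plan. If such tests followed only a significant three-group chi-square test, simulated family error would be 0.047 to 0.052 without further correction.
- *Bonferroni over three pairs is an error.* It is a valid, conventional choice.
- *Acupuncture versus suppository is not a trial question.* The Introduction stresses the combination, but the Discussion says the trial evaluates different regimens and names the two single-treatment groups.

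**Conclusion.** The stated pairwise rule for non-normal data is wrong as written. It relies on a normality assumption that the branch has rejected, and it needs a reference arm that the protocol does not designate. This conclusion rests on the text alone.

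The size rests on assumed inputs. At log-SD 1 and 40 per arm, Dunnett gives up about 10 points of power to Dunn with an upward shift (70 − 60) and about 30 with a downward shift (71 − 41). At log-SD 0.5 with an upward shift there is no loss. Applying Dunnett's critical value to all three pairs gives about 7% family error.

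The harm is therefore lost power under strong skew and an undefined set of comparisons. It is not false positives caused by skew. It falls mainly on the cytokines and other single-time-point continuous measures, not on the repeated-measures analysis of NIH-CPSI. The wording should be corrected before analysis.

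**What to change.** In 2.7, replace Dunnett's method with Dunn's test on the joint Kruskal-Wallis ranks. Adjust by Bonferroni or Holm over the same set of pairwise comparisons as the normal branch, and list that set once so that both branches test the same hypotheses.

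SPSS 25, the package named in the plan, offers Dunn's comparisons after Kruskal-Wallis. The change costs a sentence of analysis wording and affects no data collection, arm or objective. No downside was identified beyond the rewording itself.
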